### Eligibility criteria {10}

#### Inclusion criteria

Age ≥ 18 yearsWritten informed consent provided by the patient or by patient’s family memberPositive reverse transcriptase-polymerase chain reaction (RT-PCR) for influenza A and/or B on a respiratory tract specimenParticipant requiring hospitalizationNational Early Warning Score 2 (NEWS2) of ≥4 at planned randomization

#### Exclusion criteria

Ongoing pregnancy or breastfeedingKnown contraindication to baloxavir or to placeboParticipant weighting <40 kgPrior treatment with influenza antiviral for the current influenza episode (NAI therapy for >24 h at the time of randomization or one dose of baloxavir)Immunosuppression defined as (1) cancer treatment with significant negative effect on the immune system as determined by study investigator; (2) immunosuppressive therapy (treatment comprising ≥20 mg/day prednisone or equivalent when administered for ≥2 weeks, biological therapies, steroid sparing drugs); (3) HIV infection if CD4+T cell count <500/µL; (4) organ or stem-cell transplantation; and (5) patients awaiting transplantSevere underlying respiratory comorbidity requiring long-term oxygen therapy at homeSevere disease requiring ICU care, need for high flow oxygen or non-invasive ventilation at the time of randomizationSevere hepatic insufficiency or any other severe medical condition when participation in the study puts the patient at risk according to the investigator’s judgmentPrior inclusion in this study during a previous influenza seasonInclusion in another interventional study with an investigational drug 30 days before or planed within 30 days after inclusion in the studyInability to consent or patient representative unable to consent

### Who will take informed consent? {26a}

Hospitalized patients with a positive RT-PCR result for influenza and requiring hospitalization are going to be screened for study inclusion and exclusion criteria. In case of study eligibility, patients will be approached by the study staff. The recruiting trial physician or nurse will explain to each patient or in case of a patient incapable of judgment to his/her legal representative the nature of the study. Those who sign the informed consent (the legal representative in case of a patient is incapable of judgment) will be included in the study and will be randomized.

### Additional consent provisions for collection and use of participant data and biological specimens {26b}

Participants will be asked to sign another separate consent for inclusion in the corresponding INFLUENT biobank resulting in further use of their clinical data and biological specimen in case of future studies. The consent also includes additional serum sampling for the biobank on the day of randomization, as well as on day 7 post-treatment administration.

## Interventions

### Explanation for the choice of comparators {6b}

Explanation for the choice of the study treatment: We chose baloxavir over oseltamivir to study the benefits of antiviral treatment: (1) to add additional treatment options to the existing choice of neuraminidase inhibitors in the hospitalized patient population, given the high mutational potential of influenza viruses and (2) due to baloxavir’s ease of use and its excellent tolerability in clinical studies [13, 16].

Explanation for the choice of the comparator: We believe that comparing baloxavir therapy to placebo in our patient population is ethical: (1) given the persisting equipoise regarding the benefits of antiviral treatment in patients hospitalized for influenza; (2) treatment should be compared to placebo in order to identify the patient population that stands to gain the most from antivirals (to further increase treatment accessibility, curtail unnecessary expenses, and mitigate the risk of emergence of resistance and adverse effects). We adapted inclusion and exclusion criteria to exclude patients who might benefit from antiviral treatment, such as the critically ill and the immunocompromised patients.

### Intervention description {11a}

A total of 484 participants will be included, with 242 randomized in each arm. In the treatment arm, participants will receive baloxavir marboxil (Xofluza®) according to their body weight (<80 kg: 1 tablet of 40 mg PO as a single dose, ≥80 kg: 2 tablets of 40 mg PO as a single dose). Participants randomized to the placebo arm will receive one single dose of placebo. The number of placebo capsules will be adapted to the patient’s weight (<80 kg: 1 capsule, ≥80 kg: 2 capsules).

### Criteria for discontinuing or modifying allocated interventions {11b}

As the intervention consists of a single dose of study treatment, discontinuation of the intervention is not applicable here. All participants will be free at any time and for any reason to withdraw from the study without having to give any explanation.

### Strategies to improve adherence to interventions {11c}

As the intervention consists of a single-dose study treatment and the primary endpoint is based on inpatient clinical data or the length of hospitalization, we do not expect any loss to follow-up. To ensure the feasibility of the 3-month telephone follow-up, for each inclusion the contact of a relative will be noted. In addition, the patient’s general practitioner may be contacted in case the participant or his/her relative is not able to provide adequate information at the 3-month follow-up visit. The study team can also review patient electronic health records to retrieve information about potential influenza complications and their treatment up to 90 days post-treatment administration.

### Relevant concomitant care permitted or prohibited during the trial {11d}

All concomitant medications are allowed except other investigational medicinal products (IMP) up to 30 days prior and after randomization. “As the secondary objectives measure baloxavir’s efficacy in decreasing the risk for severe influenza complications up to 90 days post-treatment administration, the use of other approved or experimental influenza antivirals after randomization and for 90 days post-treatment administration will be considered a deviation of the protocol.”

### Provisions for post-trial care {30}

In case of a serious adverse event unrelated to the natural course of the current influenza episode or in case of SAR and SUSAR, participants will be followed until event resolution. An insurance covering the study activities has been contracted through the sponsor’s institution, the Geneva University Hospitals.

### Outcomes {12}

#### Primary outcome

The primary outcome is time to clinical improvement (in hours), calculated from treatment administration until the measurement of a NEWS2 score ≤ 2 maintained for 24 h, or until hospital discharge, whichever comes first.

#### Secondary clinical outcomes

Clinical status severity score (from 1 to 6) on day 7 post-treatment administrationDuration of hospitalization post-treatment administration (in hours)Duration of O_2_ supplementation post-treatment administration (in hours)In-hospital clinical failure, defined as death or ICU or intermediate care unit (ICMU) admission during hospitalization or up to 30 days post-treatment administration in case of prolonged hospital stayMortality at D90Influenza-related complications occurring between D0 and D90, diagnosed by the treating physician (composite outcome defined as pneumonia, sepsis, acute lung injury or acute respiratory distress syndrome (ARDS), encephalitis/encephalopathy, myo- or pericarditis, otitis, sinusitis as well as any cardiovascular event (cardiac decompensation, myocardial infarction, or stroke))Number of antibiotic days (AD) prescribed during hospitalization or up to 30 days post-treatment administration in case of longer hospital stayQuality of life at day 90 post-treatment administration. Questionnaire type: EQ-5D-5L

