**Methods:**

This is an investigator-initiated, randomized, triple-blind, placebo-controlled, superiority, multi-center trial to assess the clinical efficacy of single-dose baloxavir in decreasing time to clinical improvement in adult immunocompetent patients hospitalized with influenza. Patients (*n* = 484) with confirmed, severe infection (NEWS2 score ≥ 4) will be recruited over three influenza seasons in four large Swiss hospitals. Primary outcome: time to clinical improvement (in hours), calculated from treatment administration until NEWS2 score ≤ 2 maintained for 24 h or until hospital discharge, whichever comes first. The primary outcome is calculated in all patients independently of the duration of symptoms at treatment administration, as well as in participants treated early (<72 h) post onset of symptoms. The main secondary outcomes are the risk of serious influenza complications, length of hospitalization, and difference in viral load at D3 post-treatment administration.

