### Participant timeline {13}

Patients will be followed up during hospitalization; data on clinical symptom severity, as well as flu complications (exacerbation of underlying disease, bacterial superinfection, need for ICU admission, death), antibiotic use, and duration of hospitalization will be collected. Nasopharyngeal swab for virological endpoints will be taken on day 0 and day 3 following treatment administration. After discharge, one phone follow-up visit is planned 90 days post-treatment administration (Table 1).

**Table 1 Tab1:** Patient timeline, screening, inclusion, treatment and follow-up schedule

**Study visit**	**1**	**0**	**2**	**3.1**	**3.2**	**3.3**	**3.4**	**3.5**	**3.6**	**3.7**	**3.8**	**3.9**	**3.10**	**4**	**5**
	**Screening**	**Consent**	**Allocation**	**In-hospital follow-up**											
**Timepoint**	Day −2 to D0	D0	D0	D1	D2	D3	D4	D5	D6	D7	D8	D9	…	Discharge day	D90
**Window (in days)**															±10
**Informed consent**		x													
**Inclusion and exclusion criteria**	x														
**Flu symptoms history**			x												
**Medical history**			x												
**Demographics**			x												
**Quality of life questionnaire**			x												x
**NEWS2 score**	x		x	1/8 h until discharge (a)											
**Clinical symptoms severity evaluation**			x	1/D until discharge											
**Influenza complications evaluation**			x	1/D until discharge											x
**6-point ordinal scale**										x					
**Serious adverse events***			x	During hospitalization											x
**Laboratory results collection**			x^b,c^	Once between D2 and D4^b,c^											
**RT-PCR NP swab**			x^d^			x^d^									
**Viral culture**			x^e^			x^e^									
**Viral type and subtype**			x												
**Screening for resistance-associated mutations**			x^f^			x^f^									
**Biobaking: serum sampling**			(x)							(x)					

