#### Clinical secondary outcomes

Status severity score at day 7 will be compared between groups using a Cochran-Mantel-Haenszel test stratified on center.

Length of stay (from treatment administration to hospital discharge) and duration of O_2_ supplementation will be compared between groups using a linear regression model adjusted on center. The Huber-White method will be used to compute a robust variance estimator of the coefficients. Depending on the number of deceased patients, competitive risk analyses may be preferred to a linear regression model. Risk of in-hospital clinical failure will be compared between groups using a Cochran-Mantel-Haenszel test stratified on center. Risk difference and relative risk stratified on center will be estimated using the Mantel-Haenszel method.

Mortality and risk of influenza-related complications at day 90 will be compared between groups using a Cochran-Mantel-Haenszel test stratified on center. Risk difference and relative risk stratified on center will be estimated using the Mantel-Haenszel method.

Mean number of antibiotic days (AD) for respiratory illness will be compared between groups using a linear regression model adjusted on center.

Quality-of-life score at D90 will be compared between groups using a linear regression model adjusted for center and quality-of-life score at baseline.

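### In-hospital clinical failure and antibiotic days are counted only until discharge, so if baloxavir shortens stay both comparisons tilt towards it; modestly for failure, and for antibiotics depending on how days are counted

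*Protocol article*

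**What the plan says.** In the protocol article, Outcomes {12}, Secondary clinical outcomes, clinical failure is "In-hospital clinical failure, defined as death or ICU or intermediate care unit (ICMU) admission during hospitalization or up to 30 days post-treatment administration". The sentence goes on to limit the 30 days to prolonged stays, so 30 days is a cap on long stays and does not extend follow-up past discharge. Antibiotic use has the same form: "Number of antibiotic days (AD) prescribed during hospitalization or up to 30 days post-treatment administration in case of longer hospital" stay. In the same list, mortality (D90) and influenza-related complications (D0 to D90) have fixed windows.

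Under Statistical methods {20a}, Clinical secondary outcomes, clinical failure is compared as a proportion with a centre-stratified Cochran-Mantel-Haenszel test. For antibiotics, "Mean number of antibiotic days (AD) for respiratory illness will be compared between groups using a linear regression model adjusted on center". Neither analysis accounts for time observed. The competing-risk alternative mentioned there applies only to length of stay and oxygen duration.

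On data collection, Participant timeline {13} says "Patients will be followed up during hospitalization; data on clinical symptom severity", with ICU need and antibiotic use in the same in-hospital list. Then: "After discharge, one phone follow-up visit is planned 90 days post-treatment administration". Table 1 assigns quality of life, complications and serious adverse events to that call, but not ICU or intermediate care admission or antibiotic days. Section {11c} adds: "The study team can also review patient electronic health records to retrieve information about potential influenza complications and their treatment up to 90 days" after dosing.

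**The concern.** Discharge ends the observation of both outcomes, and the treatment may itself change when discharge occurs. The primary endpoint runs to sustained NEWS2 improvement "or until hospital discharge, whichever comes first", and the abstract lists length of stay among its leading secondary outcomes: "The main secondary outcomes are the risk of serious influenza complications, length of hospitalization".

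Suppose two patients follow the same course and both need intensive care on day 6. The one still on the ward counts as a failure; the one discharged on day 3 does not. Likewise, if only days in hospital count, an identical 7-day antibiotic course scores 4 days for a patient who leaves on day 4 and 6 days for one who leaves on day 6. This affects survivors and comes from the window, not from how deaths are scored. At stake is whether a lower failure rate or fewer antibiotic days can be read as a drug effect in addition to a shorter stay.

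**Working it through.** **1. The plan's own figures.** Sample size {14} uses medians for time to improvement of 5.5 and 4 days, so HR = 5.5/4 = 1.375. The 30-day event probability under exponential times is 1 − exp(−ln2·30/median): 0.977 and 0.994, mean 0.986. Freedman events are (z₁₋α/₂ + z_power)²·((HR+1)/(HR−1))².
- 90% power: 422 events, 422/0.986 = 428 patients (plan: 432).
- 80% power: 315 events, 160 per arm (plan: 161).
- Power at N = 484: 93.2% (plan: 93%).

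These reproduce. They concern the primary endpoint only; no power is stated for the two outcomes here.

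**2. Direction.** With a fixed window and no drug effect, both arms have the same expectation: risk ratio 1.00, difference in antibiotic days 0. With a window ending at discharge, the arm with shorter stays has less time to accrue events or days. This follows from the definition whenever any event or antibiotic day falls between discharge and D30.

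**3. Clinical failure: illustrative size.** Assumptions: exponential stay with the improvement medians borrowed for it, λ = ln2/5.5 = 0.126 and ln2/4 = 0.173 per day, capped at 30 days; no drug effect on failure; discharge unrelated to risk.

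*Constant hazard h.* Counted risk = h/(h+λ)·(1 − e^(−30(h+λ))).
- h = 0.005: 3.7% placebo, 2.8% baloxavir, RR 0.75
- h = 0.01: 7.2%, 5.4%, RR 0.75
- h = 0.02: 13.5%, 10.3%, RR 0.76

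*Hazard halving every d days*, true 30-day risk 10% in both arms. Counted risk = ∫₀³⁰ h(t)·e^(−H(t))·e^(−λt) dt.
- d = 1: 8.5%, 8.1%, RR 0.95
- d = 2: 7.4%, 6.7%, RR 0.91
- d = 3: 6.6%, 5.8%, RR 0.89
- d = 5: 5.4%, 4.6%, RR 0.85

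True risks of 5% and 15% give nearly the same ratios. At 242 per arm, the chance of significance in favour of baloxavir is 3–7% with a falling hazard and 9–19% with a constant one, against a nominal 2.5% in that direction.

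**4. Antibiotic days, if only days in hospital count.** For a course of L days, identical in both arms, the expected days counted per treated patient are (1 − e^(−λL))/λ.
- L = 5: 3.71 placebo, 3.34 baloxavir, difference −0.36 from unrounded means
- L = 7: 4.65, 4.06, difference −0.60 likewise
- L = 10: 5.68, 4.75, difference −0.93

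With a 7-day course in half of the patients, this is 0.5 × 0.60 = 0.30 days per randomized patient. Counting part-days as whole days, a simulation gives 0.27, and 0.37 with 70% treated.

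Simulated share of trials with two-sided p < 0.05, 242 per arm, identical prescribing, 7-day course in 50% / 70% of patients (nominal 5%):

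| Assumed stay | 50% | 70% |
|---|---|---|
| Exponential, medians 5.5 and 4 d | 16–18% | 29–30% |
| The same plus 2 days in both arms | 8–9% | 13% |
| Half the effect (5.5 and 4.75 d) | 7–8% | 10–11% |
| Plus 2 days and half the effect | 6% | 7% |
| Lognormal, log-SD 0.6, medians 5.5 and 4 d | 37% | 66–67% |
| Lognormal, medians 5.5 and 4.5 d | 17% | 30% |

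In the first row, a 5-day course gives about 12% and 19%, and a 10-day course about 26% and 43%. If a course prescribed on the ward is counted in full wherever it is finished, this artefact disappears; only courses started after discharge are then missed.

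**The case against.** The strongest reply has five parts.

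- **Antibiotic wording.** The outcome refers to days *prescribed* during hospitalization, which can include a course finished at home. A reader might infer that such a course is certainly cut at discharge; the text does not settle this. The objection stands, and it leaves an ambiguity that sites could resolve differently.
- **Length-of-stay input.** The 4 and 5.5 day medians and the 36 h difference are for time to improvement. The plan states no effect size for stay, and stay cannot be shorter than time to improvement. Used as stay, the exponential model sends 16% and 12% of patients home within 24 h of dosing, although all enter with NEWS2 of at least 4. This stands, which is why the table varies stay.
- **Clinical failure.** A reader might infer that shortening stay would by itself produce a marked apparent reduction. That needs discharged patients to carry the same risk as those on the ward. Events probably cluster early and discharge selects the recovered, so the true artefact may be below even the falling-hazard figures.
- **Existing cover.** A reader might think deaths after discharge are lost. D90 mortality captures them, and the D0 to D90 complications outcome captures part of the morbidity. Neither records ICU or intermediate care admission as such.
- **Label and rank.** The failure outcome is openly called in-hospital, neither outcome is named among the abstract's main secondary outcomes, and no claim of independent benefit is planned. This limits the severity, but the label does not make the arms comparable.

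**Conclusion.** The point holds in a limited form. Both outcomes have a window that treatment can shorten, both are compared without regard to time observed, and the resulting bias favours baloxavir if stay is shortened. If stay is unaffected, there is no artefact from this source.

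For clinical failure the effect is probably modest, and the uncovered part is mainly ICU or intermediate care admission after discharge. For antibiotic days it depends first on the counting rule. If only in-hospital days count, false significance for a 7-day course in 50–70% of patients is about 6–7% with longer stays and half the effect, 17–30% with exponential stay at the plan's improvement medians, and higher with less skewed stays. No single figure should be quoted as the size, because stay distribution, course length and prescribing rate are all assumed.

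The documents do not support reading this as a flaw in the primary endpoint or the sample size. It is a change that should be made to two secondary outcomes.

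**What to change.** Use one window for every participant, regardless of discharge or transfer:

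- **Clinical failure:** death or ICU/intermediate care admission from dosing to D30, in any hospital.
- **Antibiotic days:** all days of antibiotic therapy from dosing to D30, including courses continued after discharge. State whether all antibiotics count or only those for respiratory illness, since the outcome definition and the analysis section differ on this.

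Keep the in-hospital versions as descriptive. Sources for the post-discharge part are the discharge letter, the record review allowed in {11c} with its contacts to a relative and the general practitioner, and the D90 call.

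The cost is revised outcome wording, a few e-CRF fields, and added items in the record review and the call. The review is currently optional and covers complications and their treatment, so it must be extended to these items. Participants already discharged can be completed from records where available. The main downside is that post-discharge antibiotic days will rest partly on prescriptions and recall, and so be less exact than ward data. N = 484 and the primary analysis do not change.

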#### Secondary virology outcomes

Detection of RNA in respiratory sample on day 3 post-treatment administrationInfectious viral load in respiratory sample at day 3 post-treatment administration

### Participant timeline {13}

Patients will be followed up during hospitalization; data on clinical symptom severity, as well as flu complications (exacerbation of underlying disease, bacterial superinfection, need for ICU admission, death), antibiotic use, and duration of hospitalization will be collected. Nasopharyngeal swab for virological endpoints will be taken on day 0 and day 3 following treatment administration. After discharge, one phone follow-up visit is planned 90 days post-treatment administration (Table 1).

**Table 1 Tab1:** Patient timeline, screening, inclusion, treatment and follow-up schedule

**Study visit**	**1**	**0**	**2**	**3.1**	**3.2**	**3.3**	**3.4**	**3.5**	**3.6**	**3.7**	**3.8**	**3.9**	**3.10**	**4**	**5**
	**Screening**	**Consent**	**Allocation**	**In-hospital follow-up**											
**Timepoint**	Day −2 to D0	D0	D0	D1	D2	D3	D4	D5	D6	D7	D8	D9	…	Discharge day	D90
**Window (in days)**															±10
**Informed consent**		x													
**Inclusion and exclusion criteria**	x														
**Flu symptoms history**			x												
**Medical history**			x												
**Demographics**			x												
**Quality of life questionnaire**			x												x
**NEWS2 score**	x		x	1/8 h until discharge (a)											
**Clinical symptoms severity evaluation**			x	1/D until discharge											
**Influenza complications evaluation**			x	1/D until discharge											x
**6-point ordinal scale**										x					
**Serious adverse events***			x	During hospitalization											x
**Laboratory results collection**			x^b,c^	Once between D2 and D4^b,c^											
**RT-PCR NP swab**			x^d^			x^d^									
**Viral culture**			x^e^			x^e^									
**Viral type and subtype**			x												
**Screening for resistance-associated mutations**			x^f^			x^f^									
**Biobaking: serum sampling**			(x)							(x)					

a: 1/8 h up to 10 days. If hospitalization is longer and the primary endpoint is still not reached, decrease NEWS2 score measurements to 1/day up to discharge. b: only if requested by the treating physician. c: only CRP and white blood cell count will be collected and only twice during hospitalization, first at D0 and second if available between D2 and D4. d: ±1 day. e: only if RT-PCR positive with CT value compatible with viral growth (CT value < 30). f: depending on budget availability. (x): 6 ml, only at HUG, only consenting participants accepting blood sample collection for future research, timepoint of collection ± 1D. *: All SAE will be collected and reported in the annual safety report. SARS and SUSAR will be reported timely to the regulatory authorities

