### Sample size {14}

Our hypothesis is that baloxavir treatment in adult, immunocompetent patients hospitalized for influenza will shorten the time to clinical improvement by at least 36 h compared to placebo. This 36-h difference was chosen as the minimal time difference considered to have a meaningful impact on clinical care. The median time to clinical improvement, in patients who received antivirals in a large clinical study, was about 4 days (97.5 h) [16]. The addition of the 36-h difference equals a time to clinical improvement of 5.5 days in the placebo group.

Two sample size calculations were performed. Sample size calculation no. 1 concerns all patients hospitalized for influenza (regardless of symptom duration at treatment administration): under the constant and proportional hazard assumption, median times to clinical improvement of 5.5 days in the placebo group and 4 days in the baloxavir group correspond to a hazard ratio of 1.375. With a follow-up period of 30 days, we calculated that a total number of 432 participants (216 per arm) would provide the trial with at least 90% power to detect such a baloxavir effect on time to clinical improvement at a two-sided significance level of 0.05.

Sample size calculation no. 2 concerns the subgroup of patients hospitalized for influenza with symptoms evolving for less than 72 h: under similar hypothesis (median times to clinical improvement of 5.5 days in the placebo group and 4 days in the baloxavir group, corresponding to a hazard ratio of 1.375 under the constant and proportional hazard assumption, and a follow-up period of 30 days), we calculated that a sample of 161 patients per arm would provide 80% power to detect a baloxavir effect in a subgroup analysis, at a two-sided significance level of 0.05. Assuming two out of three patients will present symptoms evolving for less than 72 h (ratio of 2:1), the study will need to include a total of 484 patients. With that sample size, the study will reach a power of 93% in the general population of hospitalized patients.

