#### Virology secondary outcomes

Proportion of patients with detectable RNA on day 3 post-treatment administration will be described using counts and percentages.

Proportion of patients with RNA detection and proportion of patients with an infectious viral load at day 3 post-treatment will be compared between groups using a Cochran-Mantel-Haenszel test stratified on center.

RNA and infectious viral load on day 3 (expressed in CT value and copies/ml and viral titer) will be compared between the two groups using a linear regression model adjusted for center and baseline viral load.

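### The only follow-up swab is scheduled in hospital at D3 ±1 day, so patients who leave before D2 have no virology sample; taking it before departure is a cheap improvement

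*Protocol article*

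**What the plan says.** All references are to the protocol article.

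- **Sampling times.** Participant timeline {13}: "Nasopharyngeal swab for virological endpoints will be taken on day 0 and day 3 following treatment administration". The Table 1 footnote to the RT-PCR swab allows ±1 day, so D2 to D4.
- **Where the D3 visit sits.** In Table 1, D3 is visit 3.3 under "In-hospital follow-up". The text introduces the schedule with "Patients will be followed up during hospitalization". The discharge-day column contains no swab.
- **After discharge.** "After discharge, one phone follow-up visit is planned 90 days post-treatment administration". No home or outpatient swab is described.
- **Use of the sample.** The abstract lists "difference in viral load at D3 post-treatment administration" among the main secondary outcomes. Under Virology secondary outcomes, "Proportion of patients with RNA detection and proportion of patients with an infectious viral load at day 3 post-treatment will be compared between groups" by a Cochran-Mantel-Haenszel test stratified on center, and "RNA and infectious viral load on day 3 (expressed in CT value and copies/ml and viral titer) will be compared between the two groups" by linear regression adjusted for center and baseline load.
- **Missing data.** Section {20c} speaks only of the primary outcome.
- **Discharge.** It is one of the two ways to reach the primary endpoint (Outcomes {12}). Transfer to another hospital counts as discharge for that endpoint ({18a}).

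**The concern.** Having a D3 sample depends on still being in hospital around D3, and that is a post-randomisation event. The trial's hypothesis is that baloxavir brings improvement forward, and discharge is part of that endpoint. If the hypothesis is true, more baloxavir than placebo patients are likely to have left before the swab. Those who remain are slower recoverers, and more strongly selected as such in the baloxavir arm. If slow clinical recovery goes with slow viral clearance, the comparison among sampled patients understates the antiviral effect.

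The ±1 day window narrows the loss but has a side effect. Patients about to leave may be swabbed on D2 instead of D3, more often on baloxavir. If load is still falling, that also works against the drug.

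At stake are the virology comparisons, one of which is named a main secondary outcome. The clinical primary and co-primary analyses do not use the swab.

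**Working it through.** **1. Inputs from Sample size {14}.** The plan assumes "median times to clinical improvement of 5.5 days in the placebo group and 4 days in the baloxavir group", constant and proportional hazards, HR 1.375, 30 days of follow-up, and 242 per arm.

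**2. The plan's own figures reproduce.** The mean probability of the event within 30 days is [(1 − 2^(−30/5.5)) + (1 − 2^(−30/4))]/2 = 0.986. Freedman's formula, d = (1.960 + 1.282)² × (2.375/0.375)², gives 422 events. That is 215 per arm, or 430 in total, against the stated 432. At N = 484, power is 93.2% against the stated 93%. The medians can therefore be carried forward as the plan's working model.

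**3. Share at improvement or discharge by time t,** p = 1 − 2^(−t/median):

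| t | Placebo | Baloxavir | Gap | Patients of 242 (placebo / baloxavir) |
|---|---|---|---|---|
| 48 h | 1 − 2^(−2/5.5) = 22.3% | 1 − 2^(−2/4) = 29.3% | 7.0 points | 54 / 71 |
| 72 h | 1 − 2^(−3/5.5) = 31.5% | 1 − 2^(−3/4) = 40.5% | 9.1 points | 76 / 98 |

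Under the plan's model these bound the number of missing swabs from above, because the endpoint can also be reached in hospital by a sustained low NEWS2. The documents give no discharge-time distribution, so the share *f* of these patients who have left unswabbed is an assumption. With f from 25% to 100%, losses are 13-54 (placebo) against 18-71 (baloxavir) at the 48 h cut, and 19-76 against 25-98 at the 72 h cut.

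**4. Effect on the difference in D3 load.** Assumptions, none of them from the documents: a true difference of 0.5 log10, SD 1 log10, and a correlation ρ of 0.3 to 0.5 (Gaussian copula) between slow exit and high D3 load. If a random fraction f of those at the endpoint is lost, the mean load of the sampled patients rises by ρ × SD × f·φ(Φ⁻¹(p))/(1 − f·p). The true difference shrinks by the gap between arms in this quantity.

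For f = 1 at 48 h:
- placebo: 0.2982/0.7772 = 0.384
- baloxavir: 0.3439/0.7071 = 0.486
- gap: 0.103; times ρ = 0.031 to 0.051 log10, or 6-10% of 0.5

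For f = 1 at 72 h:
- placebo: 0.3551/0.6852 = 0.518
- baloxavir: 0.3877/0.5946 = 0.652
- gap: 0.134; times ρ = 0.040 to 0.067 log10, or 8-13%

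The same formula with partial loss:

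| Share f lost | 48 h cut | 72 h cut |
|---|---|---|
| 25% | about 1% | about 1% |
| 50% | 2-3% | 2-3% |
| 100% (upper bound) | 6-10% | 8-13% |

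A simulation of this model agrees. Allowing for Monte Carlo variation between runs, the ranges are about 0-4% for partial loss and 6-13% at the bounds. The percentages scale with the SD: 2 log10 instead of 1 would double them.

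**5. In proportion.** The standard error of the difference with all 242 per arm is √(2/242) = 0.09 log10. The partial-loss shifts are at most about 0.02 log10. Loss of samples is the other cost: at the bounds, (54 + 71)/484 = 26% and (76 + 98)/484 = 36%, and half or less of that in the partial-loss cases.

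**The case against.** The strongest counter-argument is that the loss is small and partly avoidable already. The window lets anyone still present on D2 be swabbed. Many endpoints will be reached in hospital. Constant hazards are a sample-size convenience, not a discharge forecast for inpatients with NEWS2 of at least 4. This stands, and it is why the upper-bound percentages should not be read as expected values.

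Three stronger readings are tempting, and the documents do not support them:

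- *Every patient who recovers before D3 drops out of all virology comparisons.* The D2 window contradicts this, and so does improvement without discharge. That sampling is confined to inpatients is itself inferred from the Table 1 block and the phone-only follow-up. The sentence on swab days carries no such condition.
- *Clinical and virological results could be made to disagree.* Shifts of up to about 0.02 log10 against a standard error of about 0.09 do not carry that.
- *The analysis will be complete-case.* The article names tests and models and does not say how absent D3 values are treated. An analysis plan not shown may settle that, so its absence here is no fault.

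What the objection does not remove is the schedule. An analysis plan can impute, but it cannot recover a sample that was never scheduled. Nor is this a case of the article omitting detail, since it prints the visit table with its window and sampling footnotes.

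**Conclusion.** The point holds as a cheap improvement of low to moderate priority. As scheduled, patients discharged or transferred before D2 have no follow-up sample. Those leaving on D2 or early on D3 have one only if someone brings the swab forward. If baloxavir speeds discharge, missing and early samples will be more frequent in that arm.

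The expected effect is a modest pull toward no difference: about 0-4% of a true 0.5 log10 if 25-50% of those at the endpoint have left unswabbed, and 6-13% only if all of them have. The direction rests on early leavers clearing virus faster. The size rests on the assumed SD, correlation and share lost, and the actual share cannot be derived from the documents.

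**What to change.** **Schedule (Table 1, D3 swab).** Add: *if discharge or transfer is planned before the D3 swab, take it before the patient leaves and record the time.*

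**Analysis (here or in the analysis plan).**
- Count samples within the existing ±1 day window as D3 samples.
- Do not treat samples taken before D2 as D3 values. Use them as auxiliary information, with arm, baseline load and NEWS2 course, in multiple imputation of the D3 value.
- Keep sampling time for a sensitivity analysis. As a covariate in the main model it would depend on post-randomisation discharge, and it would not turn a D1 sample into a D3 one.
- Report the numbers of missing and early swabs by arm.

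**Cost.** The same single swab is moved forward for early leavers, with no added visit, plus a line of protocol text and modest analysis work. The downside is that early leavers contribute an earlier sample, and for those sampled before D2 the D3 result relies on the imputation model. Recruitment is planned until after the 2026/2027 season (Trial status), so the change can still help future participants. Swabs already missed cannot be recovered.
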